| Random 1:1               | 
Arm A (Intervention): COVID-19 Convalescent Plasma (CCP) in addition to standard therapy. Patients receive 3 doses (200 ml/day in 3 consecutive days) of ABO matched CCP.
 
Arm B (Control): Standard therapy with no CCP
                                                                                                                                                                                                                                                                                                                                                                                                                                                                                                                                                                                                                                                                                                                                                                                                                                                                                                                                                                                                                                                                                                                |

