## INTERVENTIONS

|                              |                                                                                                                                                                                                                                                                                                                                                                                                 |
|------------------------------|-------------------------------------------------------------------------------------------------------------------------------------------------------------------------------------------------------------------------------------------------------------------------------------------------------------------------------------------------------------------------------------------------|
| Treatment             | 
Patients will be randomized 1: 1 to receive one of the following treatments
 
 
– Arm A (Intervention): Standard therapy with COVID-19 Convalescent Plasma (CCP). Patients in this arm receive three consecutive doses (200 ml/day for 3 days) of ABO matched CCP.
 
– Arm B. (Control): Standard therapy with no CCP
 
 |
| Stopping rule         | 
The study will be discontinued if 6 (10%) trial participants in the arm A will have a severe adverse event connected with plasma infusion (Appendix B).
                                                                                                                                                                                                                                  |
| Concomitant therapies | 
Patients enrolled in this study receive standard therapies in addition to CCP. The enrollment of participants in other interventional trials is not allowed.
                                                                                                                                                                                                                             |

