### Primary outcome

- Proportion of patients without progression in severity of pulmonary disease defined as worsening of 2 points in the ordinal scale of WHO within day 14.

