#### Screening phase: day -1

#### Baseline visit: day 0:

Physical examination and vital signs (blood pressure, heart rate, respiratory rate, temperature), Respiratory status (pO2/FiO2 and SpO2 at rest if applicable), ECG; blood sampling for ABO groups (on two separate samples), RT-PCR for SARS-CoV-2 on nasopharyngeal swab. routine blood tests (blood count, creatinine, BUN, sodium, potassium, ALT, AST, LDH, fibrinogen, D-dimer, ferritin, CRP), viremia, anti SARS-Cov-2 antibody screening, IL6.

**Plasma administration: days 1,2, 3.** All patients will sign the informed consent to receive blood products in use at each center.

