**Secondary endpoints**

Descriptive results will be presented as means  $\pm$  standard deviation (SD), medians with interquartile range (IQR), and percentages with 95% confidence intervals (CI). Chi-square or Fisher's exact test will be used to compare categorical variables. ANOVA and Student's t-test will be used for continuous variables unless they will be not normally distributed, in which case the Kruskal-Wallis or Mann-Whitney test will be used to compare continuous parameters. Kaplan-Meier product-limit estimates will be used to calculate time to different secondary endpoints. The log-rank test will be used to assess the difference between the survival curves among arms. Changes in some biomarkers respect to baseline values will be compared using paired Wilcoxon test. The association between primary outcome and transfusion dose of CCP expressed as ml/kg of the recipient body weight, adjusted for anti-Sars-CoV-2 neutralizing and ELISA antibody concentrations, will be investigated through regression analysis. All tests will be two-sided and a P value inferior to 0.05 will be regarded as significant.

**Analysis settings** Analysis will be carried out in the "intention to treat" set.

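### With a fixed 600 ml in arm A, the planned ml/kg regression cannot estimate a dose-response, whichever patients it includes

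*Protocol*

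**What the plan says.** The Protocol gives arm A one volume whatever the patient's weight. The synopsis says "Patients receive 3 doses (200 ml/day in 3 consecutive days) of ABO matched CCP", and Interventions repeats it: "Patients in this arm receive three consecutive doses (200 ml/day for 3 days) of ABO matched CCP". The visit schedule gives "Plasma administration: days 1,2, 3". Arm B is "Standard therapy with no CCP".

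Statistical methods, Secondary endpoints, then sets out the dose analysis: "The association between primary outcome and transfusion dose of CCP expressed as ml/kg of the recipient body weight". The method is a regression, and the only covariates it names are antibody levels measured by neutralisation and by ELISA. The same paragraph ends: "All tests will be two-sided and a P value inferior to 0.05 will be regarded as significant". The outcome is the primary one: absence of progression, "defined as worsening of 2 points in the ordinal scale of WHO within day 14".

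Analysis settings names the intention-to-treat set for the analyses in general. Nothing says whether this regression covers arm A alone or both arms with arm B at 0 ml/kg. Nor is it said whether the antibody concentrations are those of the transfused plasma or of the recipient.

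**The concern.** A dose-response regression needs doses that differ for reasons unrelated to prognosis. Here the prescribed volume does not differ at all. Dividing by weight turns a constant into a measure of body size, and body size may carry prognosis of its own. The Protocol lists obesity (BMI of 40 or more) among the risk comorbidities in Appendix A and describes poor-prognosis patients in the Rationale as older and mostly male. Sex and age are related to weight.

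The second source of variation is infusions not given. Infusions fall on days 1 to 3, inside the 14-day outcome window. A patient who worsens on day 1 or 2 and then misses an infusion gets a low dose because of the outcome, which is reverse causation. Adjusting for antibody concentrations removes neither problem.

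At stake is the reading of one secondary result: a P value below 0.05 would be called significant for dose when plasma dose had no effect. The exposure, the covariates and the threshold are all fixed in the Protocol, so this is not merely a detail left for an analysis plan.

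**Working it through.** **Plan's own figures.** The Protocol gives no figure for this regression. The only size used here is the phase III one, 91 per arm. The two-proportion formula with continuity correction (20% v 40%, two-sided alpha 0.05, power 80%) reproduces it: 91. For phase II (alpha 0.2) it gives 56 against the stated 57. The odds ratio is (0.2/0.8)/(0.4/0.6) = 0.375, as stated.

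**Step 1: what the exposure measures.** Dose = 200 x (infusions received) / weight.

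| Weight | 3 infusions | 2 infusions | 1 infusion |
|---|---|---|---|
| 50 kg | 12.0 ml/kg | 8.0 | 4.0 |
| 75 kg | 8.0 | 5.3 | 2.7 |
| 100 kg | 6.0 | 4.0 | 2.0 |

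Among fully treated patients, dose = 600/weight, so its correlation with 1/weight is exactly 1. Small differences in unit volume are ignored.

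**Step 2: arm A only, no plasma effect.** The inputs are assumptions, not Protocol figures: 91 patients, weight Normal with mean 76 kg and SD 15, 20% progressing, logistic regression of progression on ml/kg. Rate of P<0.05 for the dose term:

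| Setting | False-positive rate |
|---|---|
| Weight not prognostic, no missed infusions | about 5% |
| Progression OR 1.2 per 10 kg | about 13% (11% to 17% across repeat runs) |
| OR 1/1.2 per 10 kg (low weight is worse) | about 16%, in the opposite direction |
| Weight neutral, 10% of progressors miss 1 or 2 infusions | about 16% (14% to 16%) |
| OR 1.2 and 10% of progressors missing | about 38% (38% to 41%) |

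A second model assumed mean weights of 80 kg (men) and 68 kg (women), SD 12, 30% progressing, and an antibody covariate in the regression. It gave 16%, 44% and 71% for OR 1.2, 1.4 and 1.6 per 10 kg, and 18% and 48% when 10% and 20% of progressors missed infusions. A sex effect alone (OR 2) gave only 8%. With the phase II size of 57 in arm A, OR 1.4 gave 27%.

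**Step 3: arm B included at dose 0.** Under the step 2 settings the false-positive rate falls to 4% to 7%. The second model gives 7.5% (OR 1.4) and 8% (20% missing). The reason is that the exposure now varies mainly between arms. With a true effect of the planned size the same term is significant in 88% of trials, which is essentially the randomised comparison showing through.

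**Step 4: can adjustment rescue it?** Adding weight to the arm A model restores the level (4.5% and 3.8% at OR 1.4 and 1.6). But weight and 600/weight correlate at -0.97, a variance inflation factor of about 16, so almost no separate dose information is left.

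The alternative is an arm by 600/weight interaction in both arms, using assigned volume. It holds its level at 4% to 6%. Its power can be checked by hand. A linear dose effect that takes progression from 40% to 20% at 76 kg (the phase III wording) is ln(0.375)/(600/76) = -0.981/7.89 = -0.124 per ml/kg. The simulated standard error is about 0.24, so z = 0.124/0.24 = 0.52. Power = P(Z > 1.44) + P(Z < -2.48) = 0.075 + 0.007, or about 8%.

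**The case against.** The strongest reply concerns scope. The Protocol does not restrict this regression to arm A, and its general rule is intention to treat, which read literally brings in arm B at zero dose. The false-positive rate is then close to nominal. This stands, and a reader who infers that the Protocol commits to a test with a 13% to 40% error rate goes too far. It does not save the analysis, because in that reading the coefficient is not a dose-response estimate. If the antibody covariates are those of the transfused units, they are also undefined in arm B, which would point back to arm A.

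A reader might also infer that the bias would make more plasma per kilogram look protective. The documents do not support a direction. The obesity entry covers only a BMI of 40 or more and is one of 14 qualifying conditions. Older, frailer patients of low weight would push the other way. No passage says that deteriorating patients miss infusions, so the missed-infusion rate is an assumption too.

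Finally, this is a secondary analysis described as an association. A reader might see a threat to the trial's main conclusion, or expect weight-based dosing to follow from the result. Neither is supported: the Fisher test, the condition for starting phase III and the sample size do not use this regression, and no dosing decision is tied to it.

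**Conclusion.** The point holds within those limits. The planned ml/kg regression cannot answer a dose question under either reading. In arm A alone it is confounded by body size and open to reverse causation, with a false-positive rate of about 13% to 40% under moderate assumptions, higher under stronger ones, and in an unknown direction. With arm B at zero it is nearly valid as a test of no effect, but it tests the arm difference rather than dose.

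The structural argument rests on Protocol text alone: fixed volume, ml/kg exposure, antibody-only adjustment, and infusions inside the outcome window. The percentages rest on assumed weight distributions, odds ratios and missed-infusion rates. The change is worth making, but it concerns one secondary analysis only.

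**What to change.** State the analysis set, label the analysis exploratory and non-causal, and say that the ml/kg coefficient will not be read as dose-response.

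If a dose analysis is kept:

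- Define dose as assigned volume over baseline weight (600 ml/weight). Fit both arms with arm, 1/weight, age group and sex, and test the arm by 1/weight interaction. Arm B then supplies the effect of weight itself, and missed infusions cannot enter.
- Where titres of the transfused units are available, use their antibody content as the exposure within arm A in place of ml/kg, with baseline weight, age and sex as covariates. The plan already adjusts for antibody concentrations. The benefit/risk section notes, however, that no validated commercial assay for neutralising titre existed at the time of writing, so this depends on assays becoming available.

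The cost is wording, plus making explicit that baseline weight is recorded: ml/kg already requires it, but the baseline visit list does not name it. The statistical price is a very wide interval. With about 8% power for a dose effect of the planned size, a null interaction is not evidence against a dose effect. The interaction also cannot separate dose from weight modifying the effect of plasma. A fixed-volume design carries almost no dose information, and the text should say so.

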**METHODS: MONITORING**

**Data monitoring** Each study site agrees to allow monitors from Monitoring Unit of Fondazione Policlinico Gemelli (FPG) IRCCS direct access to the study records and medical records from those patients enrolled in the clinical study. In accordance with the applicable regulations and good clinical practice (GCP), the monitor shall periodically contact the center. The

duration, nature and frequency of such visits/contacts shall depend on the rate of recruitment, the quality of the documents in the possession of the center, and its adherence to the protocol.

Through these contacts, the monitor must: control and evaluate the progress of the study, examine the collected data, conduct Source Document Verification (SDV), identify every problem and find solutions.

The aims of the monitoring activity are to verify that: the rights and well-being of the subject are respected, the study data are accurate, complete and verifiable by original documents and the study is conducted in accordance with the protocol and any approved amendments, GCP and the applicable regulations.

## **ETHICS AND DISSEMINATION**

|                                      |                                                                                                                                                                                                                                                                                                                                                                                                                                                                                                                                                                                                                                                                                                                   |
|--------------------------------------|-------------------------------------------------------------------------------------------------------------------------------------------------------------------------------------------------------------------------------------------------------------------------------------------------------------------------------------------------------------------------------------------------------------------------------------------------------------------------------------------------------------------------------------------------------------------------------------------------------------------------------------------------------------------------------------------------------------------|
| Research ethics approval      | The study will be conducted with the approval of the Ethics Committee, after verification of compliance with the European Union Clinical Practice Standards and in accordance with ICH Good Clinical Practice (GCP) and the ethical principles expressed in Declaration of Helsinki. The study will be carried out adhering to local legal requirements and the applicable national law, whichever represents the greater protection for the individual. Study protocol, patient information and informed consent will be submitted to the appropriate Ethical Committee for approval. Will inform the Ethical Committee about any changes in the study protocol which could interfere with the patient's safety. |
| Protocol amendments           | Any protocol amendments will be communicated (e.g., changes to eligibility criteria, outcomes, analyses) to investigators, EC/IRBs, trial participants, trial registries, and regulators.                                                                                                                                                                                                                                                                                                                                                                                                                                                                                                                         |
| Informed consent for patients | The participant, adequately informed in clear, simple and understandable words of the technical terms used, will be invited to provide written informed consent. The participant will be provided with a description of the general aims of the research, the methodology and procedures used, the indication of any benefits or possible risks and adverse effects. In addition to the consent to participate to the study, all patients will sign the consent to receive blood products in use at each center. The physicians treating the hospitalized patient are responsible for information of the patient and obtaining of the Informed Consent. The consent will be                                       |

expressed orally: two different witnesses will state that the patient was properly informed and fully understood study aim and procedures, and will sign the consent. In the event that the interested party revokes consent to the processing of data for research purposes, the biological sample taken for such purposes would also be destroyed. Blood samples will be collected during routinely performed samples during the investigations necessary for the pathology in progress. Participation in the research will not entail any additional costs for the participant. Should a medical problem arise due to the study, the participant will be provided with the most appropriate treatment. In accordance with the law on the protection of personal data (Legislative Decree 30/6/2003 No. 196, Guidelines for the processing of personal data in the context of clinical trials of medicinal products - 24 July 2008 - OJ No. 190 of August 14, 2008; 2016/679 European Regulation, as well as the Deliberation of the Guarantor (Del.52 of 24/7/08) will be specified that the centers of experimentation in accordance with the responsibilities established by the rules of good clinical practice (legislative decree 211/2003), will process personal data, especially those on health and, only to the extent that they are indispensable in relation to the objective of the study, other data related to the demographic characteristics, exclusively according to the realization of the study.

The informed consent for patients is provided in Appendix F.

**Informed consent  
for donors**

An informed consent, asking for their availability to be contacted by the medical staff of transfusion centers, will be provided to patients not enrolled in this study who are discharged from hospital after COVID-19. These patients will be informed about the possibility to donate their plasma and modalities of plasma donation. If they agree to participate to the study, they will be contacted after discharge and plasma donation will be arranged if their donor suitability will be confirmed.

The informed consent for patients is provided in Appendix G.

**Confidentiality**

All subject related information including Case Report Forms, laboratory specimens, evaluation forms, reports, etc. will be kept strictly confidential. All records will be kept in a secure, locked location and only research staff will have access to the records. Subjects will be identified only by means of a coded number specific to each subject. All computerized databases

will identify subjects by numeric codes only, and will be password protected.

Upon request, subject records will be made available to the study audit, monitoring representatives of the study promoter, or representatives of regulatory agencies (CNS).

**Access to data**

Only people officially registered as study investigators or data managers will receive a user login to access the REDCap web platform and enter/manage data. Source documentation should support the data collected on the CRF's. Source documents include all recordings of observations or notations of clinical activities and all reports and records necessary for the evaluation and reconstruction of the clinical

**Insurance**

After study approval by EC, the sponsor will stipulate an insurance policy with Lloyd's Insurance Company S.A to cover all risks connected with plasma therapy.

**Dissemination  
policy**

Investigators and sponsor will communicate trial results to participants, healthcare professionals, and the public through scientific publications. Authorship eligibility will be defined according to ICMJE guidelines.

**APPENDICES**

**APPENDIX A**

**LIST OF COMORBIDITIES**

- a. Chronic cardiac disease
- b. Hypertension
- c. Metastatic solid tumors
- d. Chronic pulmonary disease
- e. Malignant neoplasm (including leukemia & lymphoma)
- f. AIDS/HIV
- g. Chronic kidney disease requiring dialysis
- h. Obesity (BMI≥40)
- i. Liver disease
- j. Diabetes (with or without complications)
- k. Rheumatologic disorder
- l. Chronic neurological disorder
- m. Hemiplegia
- n. Paraplegia

## APPENDIX B

### ADVERSE/SEVERE ADVERSE EVENT: DEFINITIONS AND MANAGEMENT

**Adverse Events** An ‘adverse event’ is defined in Article 2 (m) of Directive 2001/20/EC as follows: ‘Any untoward medical occurrence in a patient or clinical trial subject administered a medicinal product and which does not necessarily have a causal relationship with this treatment’. An adverse event can therefore be any unfavorable and unintended sign (including an abnormal laboratory finding, for example), symptom or disease temporally associated with the use of a medicinal product, whether or not considered related to the medicinal product

An “adverse event” is any worsening in the general condition of a subject, or a subject participating in a clinical experiment to whom a pharmaceutical product is administered, regardless of its relationship with the given treatment. An AE may also be any unexpected adverse sign (which can include an abnormal laboratory result of clinical significance), and each symptom or pathology temporarily associated with the use of a pharmaceutical product, regardless of its relationship with the same product. AEs may be **expected** (consistent with the information leaflet provided with the product) or **unexpected** (inconsistent with the information available).

